### Outcome measures

Cognitive status will be assessed using the Brief International Cognitive Assessment for MS (BICAMS) and the Paced Auditory Serial Addition Test (PASAT) with 3- and 2-second intervals. The BICAMS battery includes the Symbol Digit Modalities Test (SDMT), the California Verbal Learning Test, 2nd edition (CVLT-II), and the Brief Visuospatial Memory Test-Revised (BVMT-R). All instruments are widely used in cognitive assessment of PwMS. Patients scoring below the 5th percentile of age-, sex-, and education-adjusted norms in at least two of these tests will be eligible. Additional secondary outcomes will include self-reported measures of mood, fatigue, and quality of life: Multiple Sclerosis Quality of Life (MSQoL) [18], Beck Depression Inventory (BDI) [19], and Fatigue Severity Scale (FSS).

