### Statistical analysis and sample size

Descriptive characteristics of the included patients will be presented as mean ± standard deviation (SD) or median and interquartile range (IQR) for continuous variables and as absolute frequencies and percentages for categorical variables. Baseline characteristics of the patients will be also shown splitting the patients into the two groups of treatments and comparisons will be performed using Chi-squared test of Fisher’s exact test (for categorical variables) and Mann-Whitney U test or t-test (for continuous variables). Results of the SDMT and PASAT tests will be presented over time as Mean ± SD by showing separately the two groups of treatment. The repeated measures ANOVA will be used to assess the effect of treatment, the effect of time, and the interaction effect between time and treatment on the performance of the SDMT and PASAT tests. The sample size was calculated fixing a power of 0.80 and a significance level of 0.05 and we calculated the sample sizes required for between effect, for within effect and for the between–within interaction effects for both the neuropsychological tests, planning of picking as our final sample size the largest one. To calculate sample sizes, means of measurements over time and covariance matrix for the repeated measures were defined for the SDMT and PASAT tests based on clinical expectations and on previous findings [24]. The largest sample size was the one required for the between effect in the analysis of PASAT test, leading to a sample size of 33 patients in each group to detect the treatment effect of magnitude δ = 0.35. This sample size is even more satisfactory for the SDMT test, where a smaller sample size was required. However, assuming a drop-out rate of 20%, we finally need to enroll in 80 subjects with 40 patients per treatment group. After performing the repeated measures ANOVA, in case of presence of differences, we also plan to compare means using paired t-test, adequately adjusting for multiple testing. In case of missing data over follow-up, a multiple imputation by chained equations approach will be used with 10 imputations. Additionally, we will also perform the same analyses, using complete data to check the robustness of the results. A p value less than 0.05 will be considered significant. All the analyses will be conducted with the Statistical Software Stata version 16.0 (Stata Corporation, College Station, TX, USA). Randomization will be performed using computer-generated random numbers.

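### SDMT and PASAT are each tested for treatment and for time × treatment at an unadjusted 0.05, with no decisive outcome or effect named and multiplicity control promised only for the follow-up t-tests

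*Protocol article*

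**What the plan says.** All the relevant analysis text is in the protocol article under Statistical analysis and sample size.

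- **Tests.** The purpose of the repeated measures ANOVA is "to assess the effect of treatment, the effect of time, and the interaction effect between time and treatment on the performance of the SDMT and" (the sentence then adds the second test, PASAT). Of the three effects per outcome, treatment and time × treatment compare the arms. The time effect does not.
- **Threshold.** "A p value less than 0.05 will be considered significant". No other level is given for the ANOVA tests.
- **Sample size.** "The sample size was calculated fixing a power of 0.80 and a significance level of 0.05". A requirement was computed for the between, within and interaction effects "for both the neuropsychological tests, planning of picking as our final sample size the largest one". The largest came from the between effect on PASAT, "leading to a sample size of 33 patients in each group to detect the treatment effect of magnitude δ = 0.35".
- **Multiplicity.** If the ANOVA shows differences, "we also plan to compare means using paired t-test, adequately adjusting for multiple testing". This is the only mention of adjustment.
- **PASAT.** Outcome measures lists "the Paced Auditory Serial Addition Test (PASAT) with 3- and 2-second intervals". The analysis section refers to PASAT as one test.

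The stated primary aim, in the Abstract and the Introduction, is to look for benefit of the combined treatment. It names no outcome, effect or visit. Outcome measures ranks only the mood, fatigue and quality-of-life scales as secondary.

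**The concern.** Two outcomes with two arm-comparing effects each make four tests. All are judged at 0.05, and all stand on the same footing in both the analysis and the sample size. The promised adjustment comes one step too late: it covers comparisons made after an ANOVA result has been declared, so the tests that open the gate are not protected.

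The plan leaves room for any of the four results to be presented as showing that adding A-tDCS works. The 5% level would then describe each test but not the trial's conclusion. If the choice of decisive test is made after the data are seen, no later correction can make it credible.

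**Working it through.** **Inputs from the article.** Level 0.05 per test; power 0.80; δ = 0.35; 33 per group; four visits (baseline, end of treatment, 1 month, 6 months); two modelled outcomes; two arm-comparing effects per outcome.

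**Assumed, because the article does not give them.** Between-outcome correlation 0 to 0.8; within-patient correlation between visits 0.6; normal data with no true effect; any one significant test may support a conclusion.

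**Step 1: the plan's own figure.** The article does not define δ. Read as Cohen's f for two groups, δ = 0.35 is a standardised difference of 0.70. The F test with 1 and 64 degrees of freedom and noncentrality 66 × 0.35² = 8.085 has power 0.7997 at α = 0.05. This reproduces 33 per group, at an α that is not split across tests.

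**Step 2: four independent tests.**
- Any direction: 1 − 0.95⁴ = 0.185.
- Favouring A-tDCS (0.025 per test): 1 − 0.975⁴ = 0.096.
- One outcome with both effects, any direction: 1 − 0.95² = 0.0975.

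**Step 3: correlated outcomes.** The ANOVA was simulated under no effect, with 33 per group, four visits and 20,000 runs. An interaction counts as favouring A-tDCS when it is significant and the mean post-baseline gain is larger in the experimental group.

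| Between-outcome correlation | Two outcomes, any direction | Two outcomes, favouring A-tDCS | Three outcomes, any direction | Three outcomes, favouring A-tDCS |
|---|---|---|---|---|
| 0 | 18.5% | 9.6% | 26.6% | 14.2% |
| 0.3 | 18.5% | 9.6% | 25.3% | 13.3% |
| 0.5 | 17.6% | 9.0% | 23.5% | 12.3% |
| 0.7 | 15.9% | 7.9% | 20.9% | 10.8% |
| 0.8 | 15.0% | 7.6% | 18.8% | 9.7% |

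The three-outcome columns apply only if the two PASAT intervals are analysed separately. For six independent tests the formula gives 1 − 0.95⁶ = 0.265. A single two-sided test has 5% in either direction and 2.5% in favour of A-tDCS.

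**Step 4: what splitting α would cost.** With f = 0.35 and 33 per group, between-effect power is 0.80 at α = 0.05 and 0.707 at α = 0.025, the first step of Holm over two tests.

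**The case against.** The strongest reply is that this is a condensed article whose analysis plan is not shown, and that allocation of α and the choice of deciding term are often settled there. The modelled set is also narrow: only SDMT and PASAT are sized and tested, the self-report scales are already secondary, and pairwise comparisons are conditional and adjusted. All of that is true. It does not remove the point, because the article does not merely stay silent. It states one threshold, sizes two co-equal outcomes at full α, and places its multiplicity adjustment on the follow-up step alone.

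Several stronger readings go further than the text allows:

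- **A 15–25% chance of a false claim for A-tDCS.** Percentages of that size count significant results in either direction, including those where sham does better. The trial's hypothesis is directional, and the rate in favour of A-tDCS is about half as large.
- **Six tests as a fact.** Outcome measures says that both PASAT intervals are administered. The analysis section treats PASAT as one of two tests and does not say that the intervals are analysed separately.
- **A rule that any one result suffices.** The article states no success rule. The error rates are conditional on that reading, which the text permits but does not adopt.
- **Loss of 0.80 power if all tests must succeed.** The article makes no joint-power claim, and no such calculation supports the criticism.

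**Conclusion.** The point holds. With SDMT and PASAT counted as two outcomes, the chance of at least one false significant treatment or interaction result is about 15–18.5% in either direction. It is about 8% to just under 10% for a result favouring A-tDCS, roughly three to four times the 2.5% of one two-sided test. If the PASAT intervals are analysed separately, the figures are about 19–26% and 10–14%.

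These sizes rest on the assumed correlation range and on any one test being enough for a conclusion. The structural defect does not depend on the exact percentages: no test is designated as decisive, and the stated adjustment does not reach the ANOVA tests.

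**What to change.** Before unblinding, state in the protocol and the registry:

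1. One primary outcome, either SDMT or one specified PASAT interval, and one ANOVA effect (treatment or time × treatment), tested at 0.05.
2. The other outcome on the same effect, tested at 0.05 only if the first is significant.
3. All remaining effects, scores and visits as secondary, without confirmatory claims.
4. Whether the two PASAT intervals are analysed separately, and which one the sample size refers to.

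The ANOVA itself need not change. The cost is wording, plus the loss of independent confirmatory status for the later tests. The first test keeps its full 0.05 and no extra patients are needed: by the article's own account, 33 per group is the largest requirement over both outcomes and all effects.

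If Holm or a split of α is preferred, the power statement must be revised. With δ = 0.35 read as Cohen's f, between-effect power with 33 per group falls from 0.80 to about 0.71 at α = 0.025.

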
### Oversight and monitoring

The IRCCS Ospedale Policlinico San Martino, Genoa, will act as coordinating center, responsible for trial oversight, central randomization, data management, monitoring, and communications with the ethics committee and trial registry. Participants will be recruited at three sites (ASL3 Neurology Department, AISM Liguria Rehabilitation Service, and IRCCS Policlinico San Martino). Each site will have a principal investigator responsible for local conduct. A Steering Committee (PI, site PIs, statistician, data manager) will oversee scientific and operational aspects, including protocol amendments, recruitment, adherence, and data quality. Data will be entered into password-protected eCRFs stored on a secure institutional server, with anonymization, restricted access, and regular back-ups. Given the low-risk nature of the trial, no Data Monitoring Committee is planned; safety will be overseen by the PI and site PIs and reported to the ethics committee.

Participants will be withdrawn in case of intolerable adverse events, clinical worsening requiring treatment changes, participant request, or investigator decision for safety. Stimulation parameters will not be modified during the trial. Adherence will be promoted through flexible scheduling, continuous support, and the engaging use of exergames.

Unblinding is not anticipated but may be authorized by the PI in exceptional safety-related circumstances. In case of discontinuation or deviation, all scheduled outcome data (clinical, neuropsychological, and patient-reported) will continue to be collected and included in intention-to-treat analyses.

All adverse events (AEs), whether solicited or spontaneous, will be documented; minor AEs will be managed immediately, while serious/unexpected AEs will be reported promptly to the PI and ethics committee. Any important protocol modifications will be submitted for ethics approval and updated in the trial registry.

Personal data will be collected only for study purposes, stored securely, and anonymized for analysis/publication. The final dataset will be accessible to the PI and study team only; the sponsor has no restrictions on access. No specific ancillary or post-trial care is planned; clinical needs will be managed as per standard practice. Given the minimal risk profile of tDCS and exergames, no specific compensation beyond national regulations is planned.

Results will be disseminated via peer-reviewed journals, conference presentations, and trial registries. A lay summary of findings will be made available to participants upon request.

### Assessment of capacity to provide consent

All participants will be adults (aged 18–60 years) with a diagnosis of multiple sclerosis but without clinical evidence of severe cognitive or psychiatric impairment preventing autonomous decision-making. Before enrollment, the investigator will ensure each participant’s capacity to provide informed consent through a brief clinical interview and review of recent neuropsychological evaluations. Only individuals who demonstrated adequate understanding of the study’s aims, procedures, and potential risks were included.

The informed consent process, including capacity assessment, was reviewed and approved by the *Comitato Etico Regionale della Liguria* (Ethics Committee approval No. 447/2023 – DB id 13376). As all participants were deemed capable of providing informed consent, no surrogate consent procedures were required.

## Discussion

This project is designed to explore the synergistic effect of A-tDCS and VR-based cognitive rehabilitation in PwMS. By combining two non-conventional restorative approaches, we aim not only to improve cognitive function but also to determine whether the benefits can be sustained over time.

Previous studies have identified key brain regions implicated in attention, information processing and executive function, such as the left DLPFC, cingulate cortices, cerebellum, and parietal areas [1,25]. Our results may contribute to refining this knowledge, clarifying the neural mechanisms underlying CI in MS, and possibly pointing to new therapeutic targets.

Beyond mechanistic insights, integrating A-tDCS with exergames training may promote greater patient engagement, enhancing adherence to cognitive rehabilitation programs. Improved compliance is expected to translate into more durable rehabilitative outcomes and a tangible impact on quality of life.

We anticipate that the combined, simultaneous (on-line) use of A-tDCS and exergames will outperform VR alone (with sham stimulation) in both efficacy and persistence of effects. If confirmed, these findings would strengthen the rationale for implementing integrated neurotechnological protocols in MS rehabilitation, providing protocols that can be translated into everyday rehabilitation settings.
